#### Relevant concomitant care permitted or prohibited during the trial {11d}

Any type of concomitant or confounding care and interventions that may influence the study outcomes will not be permitted. However, massage will be administered to the participants who develop muscle soreness after exercises. The participants will be treated with compressive garments if they complain of perceived fatigue after exercise interventions [39]. If the participants are anticipated to need an analgesic or other physiotherapy interventions during the intervention phase, they will be considered ineligible and excluded from the study.

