### Eligibility criteria {10}

The inclusion criteria for the participants are as follows: age between 18 and 59 years, male or female sex, diagnosed with NSCLBP satisfying the definition provided in the European guidelines for NSCLBP management [27], and being positive for CS-related signs and symptoms [28]. Further, using the Physical Activity Readiness Questionnaire, all participants will be screened for contraindications to exercise [29]. Table 2 presents the complete inclusion and exclusion criteria.

**Table 2 Tab2:** Inclusion and exclusion criteria

Inclusion criteria	Exclusion criteria
• Persons between 18 and 59 years of age • CLBP of more than 3 months duration • Pain intensity of more than 4 on the NPRS • Clear mechanical basis of the symptoms • Positive for CS-related sign and symptoms • Cognitively intact [Mini-Mental State Examination score > 24] • Basic working knowledge of English language	• Attributable to a recognizable, known specific pathology (e.g., infection, tumor, osteoporosis, fracture, structural deformity, inflammatory disorder (e.g., ankylosing spondylitis) or cauda equina syndrome) • Participants who are contra-indicated to participate in physical activity • Participants who have undertaken any surgical procedures to spine or suffering from symptomatic spine diseases • Participants, who report acute pain within 48 h prior to the appointment • No corticosteroids or other drug therapy in the preceding 2 weeks • Participants suffering from any other chronic pain condition, high blood pressure, Raynaud’s disease, frostbite, any open cut, sore, or bone fracture, other major illness such as cancer, visual and/or hearing impairment, and psychiatric disorders • Presence of clinical signs or symptoms of radiculopathy

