#### Intervention description {11a}

All patients who report for CLBP management will be continuously enrolled in the study. They will undergo a standardized history taking for recording of their demographic details and will be screened for eligibility. The first author will conduct a complete physical assessment and neurological examination, and the presence of “red flags” will be closely monitored. The patients providing voluntary informed consent will be referred to the outpatient departments (OPDs) of the concerned study center where more detailed evaluations will be conducted.

In case of any doubt about a participant’s capacity to engage in the exercise program, they will be directed to a medical professional for an evaluation. The same process will continue until all participants have been recruited (*n* = 172). The recruited participants will then be randomized to receive one of the three exercise interventions along with patient education or patient education alone. A group comprising healthy volunteers will serve as the control group. The interventions will last for 12 weeks. Follow-up will be conducted 3 and 6 months after the intervention.

Three qualified physiotherapists (PTs) in each center will provide the interventions. All of them have a postgraduate degree in musculoskeletal physiotherapy and an average of 11 years of clinical experience. Before initiation of the study, they will attend a training session discussing the detailed treatment procedures. All PTs will be instructed to adhere to the treatment checklist provided and to complete treatment notes after each session. The participants will be instructed to avoid engaging in any other physical program during the study period and to not exercise at home during the intervention period. All the three participant groups will receive the targeted exercise interventions along with the same health education provided to group 4 participants. In order to manage time as effectively as possible, every exercise group will have 5–7 participants. The participants will be advised to continue the exercises after the treatments are over in order to support self-management.

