#### Criteria for discontinuing or modifying allocated interventions {11b}

Any changes to the protocol that may affect the conduct of the study, or the potential benefit or safety of the patient, including changes to the study’s objectives, design, patient population, sample sizes, or significant administrative aspects, will necessitate a formal amendment to the protocol after agreement from the Institutional Review Boards of the Integral University and Composite Regional Centre for Skill Development, Rehabilitation, and Empowerment of Persons with Disabilities in accordance with local regulations.

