#### Outcomes {12}

The primary efficacy endpoint will be a minimum difference of 10% change in PPT values in CPT and a difference of ≥ 20% from baseline to week 12 in the average daily score on an 11-point (0–10) NPRS. Secondary endpoints include change from baseline to weeks 12 and 24 in number sequencing subtest, Stroop neurophysiological test, isometric muscle strength of spine and hip muscles, and the WHOQOL-BREF and ODI questionnaires.

All outcome measures will be administered or translated into Hindi for those who have difficulties reading, comprehending, and understanding English. All translations will conform to the standard guidelines for translation of patient-reported outcome measures [40].

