### Participant timeline {13}

The participant timeline is presented in Table 3.

**Table 3 Tab3:** Summary of data collection

	**Enrolment**	**Baseline/assessment**	**Follow-up**	**Exit**
Subject demographics	X	X	X	X
Outcome measures	X	X	X	X
Medical history	X			
Assessment details	X	X	X	
Patient status	X	X	X	X
Events	X	X	X	X
Protocol deviations	X	X	X	X

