### Sample size {14}

The sample size was calculated based on the inhibitory effect of the CPT on the PPT, assuming a standard deviation of 100 kPa for the inhibitory effect across all three exercise groups. A sample size of 30 participants per group provides 87% power for an independent *t*-test at a 2-sided alpha of 0.05 to detect a difference in inhibition of 80 kPa [17] when assuming a minimum difference of 0.47 (equivalent to 10% change) as clinically relevant for the CPM effect [55]. Therefore, anticipating a 30% dropout rate, 43 participants will be recruited for each group.

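### The rule on concomitant care has no stated timing and, with a per-protocol primary analysis, is likely to drop randomised participants for a pain-related reason (minor)

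*Protocol article*

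**What the plan says.** All references are to the protocol article.

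- **Concomitant care {11d}.** Care that could influence the outcomes is not allowed. Massage for soreness and compression garments for fatigue after exercise are the exceptions. The section ends with the rule that participants "anticipated to need an analgesic or other physiotherapy interventions during the intervention phase, they will be considered ineligible and excluded from the study". It does not say whether this is judged before or after randomisation.
- **Eligibility {10}.** "Table 2 presents the complete inclusion and exclusion criteria". The table has no entry for anticipated analgesic or physiotherapy need. Its only drug entry looks backwards: "No corticosteroids or other drug therapy in the preceding 2 weeks".
- **Intervention description {11a}.** Screening comes before recruitment and randomisation: "They will undergo a standardized history taking for recording of their demographic details and will be screened for eligibility".
- **Discontinuation criteria {11b}.** The text under this heading concerns protocol amendments only (it begins "Any changes to the protocol that may affect the conduct of the study, or the potential benefit or safety of the patient"), so it gives no rule for a participant whose care changes during treatment.
- **Outcomes {12}.** The primary efficacy endpoint combines a 10% change in PPT with a 20% NPRS difference, the latter measured "from baseline to week 12 in the average daily score on an 11-point" scale.
- **Statistical methods {20a,b}** assign the primary outcome a per-protocol analysis. **Section {20c}** plans an intent-to-treat analysis by original group, with likelihood-based, selection and pattern-mixture models for missing data.
- **Sample size {14}.** "anticipating a 30% dropout rate, 43 participants will be recruited for each group".

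**The concern.** Needing an analgesic or extra physiotherapy is related to pain, and pain is part of the primary endpoint. If participants leave the primary analysis for that reason, each arm's mean is taken over those who managed without such care. An arm that provokes more such need loses more of its worst responders and looks better than it is.

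Unequal loss is conceivable from the protocol itself: it expects soreness and fatigue after exercise, and one of the four randomised arms receives education only.

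This does not depend on how the exclusion sentence is read. If it acts after randomisation, participants are removed directly. If it acts only at screening, the ban on outcome-influencing care remains, and a participant who later takes an analgesic has departed from protocol. The per-protocol set would then probably omit that person. Either way the primary result departs from the intent-to-treat principle stated in {20c}.

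**Working it through.** **1. The plan's own figures.** With 30 per group, a difference of 80 kPa, SD 100 kPa and two-sided alpha 0.05, power is 87.3% by the normal approximation and 86.1% by the noncentral t. The stated 87% is reproduced. 30 / (1 − 0.30) = 42.9, so 43 per group, and 4 × 43 = 172. No figure in the plan is disputed.

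**2. When does the exclusion act?**

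| Points to screening | Points to the treatment period |
|---|---|
| Need is anticipated, for a phase still ahead | The section is about care during the trial |
| The word used is ineligible, which is entry language | The two sentences before it concern effects of exercise |
| Screening precedes randomisation in {11a} | The rule is absent from the complete Table 2 |

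Nothing else in the article decides between the two columns. Screening is at least as natural a reading.

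**3. What happens to a randomised participant who comes to need such care?**

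- Treatment-period reading: excluded from the study. The 3-month and 6-month assessments are then probably not collected, although the article does not say so.
- Screening reading: still in the study but in breach of the care ban, so probably outside the per-protocol set. The article does not define that set, hence probably.

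**4. Size of the bias.** The protocol gives no removal rates, no NPRS SD and no correlations, so these are assumptions: no true difference; 43 in each of four arms; 2 removed in three arms and 4 or 9 in the fourth; the removed participants are those with the highest latent need; the correlation between that need and the pain change is 0.3 to 0.5.

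If the top fraction f is removed, the retained mean shifts by rho × phi(z) / (1 − f) SD, where z is the normal quantile cutting off f and phi is the normal density.

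- 2 of 43: f = 0.047, z = 1.68, phi = 0.0973; 0.0973 / 0.953 = 0.102
- 4 of 43: f = 0.093, z = 1.32, phi = 0.1664; 0.1664 / 0.907 = 0.183
- 9 of 43: f = 0.209, z = 0.81, phi = 0.2876; 0.2876 / 0.791 = 0.364

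False difference between arms:

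- 2 v 4: (0.183 − 0.102) × 0.3 = 0.024 SD; × 0.5 = 0.041 SD
- 2 v 9: (0.364 − 0.102) × 0.3 = 0.079 SD; × 0.5 = 0.131 SD

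A simulation (40,000 runs, zero true difference) agrees:

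| Removed per arm | rho | False difference (SD) | Pairwise t-test rejects | Any pair, Tukey |
|---|---|---|---|---|
| 2,2,2,2 | 0.3 | 0.00 | 5.3% | 5.2% |
| 2,2,2,2 | 0.5 | 0.00 | 5.3% | 5.7% |
| 2,4,2,2 | 0.3 | 0.024 | 5.3% | 5.4% |
| 2,4,2,2 | 0.5 | 0.042 | 6.0% | 6.1% |
| 2,9,2,2 | 0.3 | 0.079 | 6.3% | 6.3% |
| 2,9,2,2 | 0.5 | 0.129 | 9.2% | 9.0% |

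Repeat runs moved the percentages by up to about 0.4 points.

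- **Pain.** At an assumed NPRS-change SD of 2: 0.024 × 2 = 0.05 to 0.129 × 2 = 0.26 points. Across SD 1.5 to 2.5: 0.024 × 1.5 = 0.04 to 0.129 × 2.5 = 0.32. The plan's clinically important reduction is 2 points.
- **False positives.** Against equal removal at the same rho, unequal removal adds between 0.1 point (2 v 4, rho 0.3) and 3.3 points (2 v 9, rho 0.5) to the Tukey error rate.
- **CPM.** With an assumed correlation of 0.05 to 0.15, the simulated shift is 0.005 to 0.039 SD. At the plan's SD of 100 kPa that is 0.5 to 3.9 kPa, against the 80 kPa target. Tukey rejection stays at 5.0% to 5.4%.

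**5. Numbers.** 43 − 13 = 30, so removals within the dropout allowance cost no planned power. If 5%, 10% or 20% were lost on top of 30% dropout, 28.6, 27.1 or 24.1 per group would remain, with t-test power of about 84%, 82% or 78%.

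**The case against.** The strongest reply is that the sentence is an ordinary screening rule. It looks forward to a phase not yet begun and uses entry language. The section heading is a reporting-checklist label, and the discontinuation section shows that text under such a label need not match it. Absence from Table 2 shows an incomplete list, not a later timing. A single person does the physical assessment before referral, the treating physiotherapists are trained and work from a checklist, and audits every 6 weeks cover eligibility. Most of this stands. A reader might infer that the plan orders randomised analgesic users to be removed, or that the two centres will apply the rule differently. The documents support neither as fact.

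Second, {20c} analyses by original group and names models for data not missing at random. That is real but partial cover. Those models replace by assumption values that could be measured, and they do not restore people left out of a per-protocol set.

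Third, a reader might infer that harm data are lost. They are not, up to exit: Table 3 ("Summary of data collection") marks events, patient status and protocol deviations at exit, and section {22} documents changes in pain. At most, follow-up after exit is lost.

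Fourth, analgesics can alter PPT and NPRS directly, so screening out expected users is defensible. This also stands, and the fix keeps that screen.

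Finally, the clash between per-protocol in {20a,b} and intent-to-treat in {20c} is an issue in its own right. It matters here because it decides whether these participants count in the primary result.

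**Conclusion.** The point holds in a limited form, as a minor one. The missing timing and the gap in Table 2 are certain, but alone they call only for clarification. What holds on either reading is that randomised participants who come to need an analgesic or other physiotherapy are likely to be left out of the per-protocol primary analysis on a pain-related ground, contrary to the intent-to-treat statement.

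It would be wrong to conclude that the result is materially biased. The between-arm bias is about zero if removals are equal. Under the assumed unequal removals it is 0.05 to 0.26 NPRS points (SD 2) and 0.5 to 4 kPa for CPM. The upper end needs 21% against 5% removal, strictly of the most extreme participants, at a correlation of 0.5. Every removal rate and correlation here is assumed. The case for acting is that the better method costs almost nothing.

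**What to change.** 1. List anticipated need for an analgesic or other physiotherapy in Table 2 as an exclusion criterion applied before randomisation only.
2. State in {11d} that, after randomisation, a participant who needs such care stays in the study. Record its type, date, reason and the last dose before assessment. Modify or stop exercise if needed, and still collect the 3-month and 6-month assessments and harms.
3. Make the intent-to-treat analysis of {20c} primary for CPM and NPRS whatever such care is used, with the per-protocol analysis of {20a,b} as a sensitivity analysis. A further analysis counting users of such care as not meeting the 20% NPRS criterion is optional.

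**Cost.** A wording amendment and one line in the case report form, with no new visits or tests. The downside is that analgesic use may lower NPRS or raise PPT at assessment and so dilute contrasts between arms. The recorded use and the per-protocol sensitivity analysis would show how far.

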#### Provisions for post-trial care {30}

If this study demonstrates the efficacy of any one type of exercise intervention post-treatment and at follow-up with a significant effect size, all participants will be prescribed that intervention to maximize its acceptability and use.

#### Outcomes {12}

The primary efficacy endpoint will be a minimum difference of 10% change in PPT values in CPT and a difference of ≥ 20% from baseline to week 12 in the average daily score on an 11-point (0–10) NPRS. Secondary endpoints include change from baseline to weeks 12 and 24 in number sequencing subtest, Stroop neurophysiological test, isometric muscle strength of spine and hip muscles, and the WHOQOL-BREF and ODI questionnaires.

All outcome measures will be administered or translated into Hindi for those who have difficulties reading, comprehending, and understanding English. All translations will conform to the standard guidelines for translation of patient-reported outcome measures [40].

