**Methods:**

The trial is a randomized, controlled, multi-center study with four experimental groups and one healthy control group. Both the researchers and the people in the study will be blinded to the results. This paper describes the protocol for a trial examining the effects of 12-week individualized, twice-weekly exercise sessions lasting 30 to 60 min in persons with CLBP, who are positive for CS. Participants will be randomized to receive either patient education with motor control exercises (MCE), superficial strengthening (SS), aerobic exercises (AE), or patient education alone. Another group comprised of healthy volunteers will serve as controls. The primary outcomes are changes in CPM outcomes as measured by the cold pressor test (CPT). The secondary objectives are to evaluate executive functioning, pain, disability, quality of life, and spine muscle strength. The outcomes will be measured at 3 months and at a 6-month follow-up.

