### Trial design {8}

This is a randomized, controlled, double-blinded study determining how CPM changes in response to three types of active exercises in CS-positive CLBP patients. Participants will be randomized to undergo 12 weeks of the motor control exercise (MCE), superficial strengthening (SS), or AE combined with patient education or patient education alone. This active treatment concurrent control design will be used to demonstrate superiority of one exercise group over another. All patients will be allocated in a 1:1:1:1 ratio using random number tables. All participants will receive advice to stay active. Another no-pain control group will also be recruited. The intervention will be provided for 12 weeks. An independent assessor will collect data at baseline (t0), after intervention at 3 months (t1), and at the 6-month follow-up (t2). Outcome measures include CPT for measuring CPM, letter–number sequencing subtest in the Wechsler Adult Intelligence Scale-III Edition (WAIS-III), Stroop neurophysiological test, QoL assessed using the abbreviated WHOQOL-BREF questionnaire, isometric muscle strength of spine and hip muscles, the Oswestry Disability Index (ODI) questionnaire, and the Numerical Pain Rating Scale (NPRS). Table 1 and Fig. 1 present the study design and flowchart, respectively. The research ethics approval was granted by the Integral University, India (IIAHSR/DO/PT/2022/23), and Composite Regional Centre for Skill Development, Rehabilitation, and Empowerment of Persons with Disabilities, India (CRCL/Ph.D. Data Collection/2021–22/1556). The study is designed according to the Consolidated Standards of Reporting Trials (CONSORT) guidelines and reported according to the Standard Protocol Items: Recommendations for Interventional Trials (SPIRIT) checklist. The study will use a 5 (between subjects − type of exercise interventions: MCE vs. AE vs. SS vs. patient education vs. no-pain control) × 3 (within subjects − time: before vs. after vs. 3 months after the intervention) mixed design.

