### Primary outcome measure

#### CPM

The CPT will be used to measure CPM. For the conditioning stimulus, the participants’ non-dominant hand will be immersed in a bucket with temperature-controlled cold water (1 °C–4 °C), monitored by a thermometer for up to 1 min. The participant has to remain with the hand immersed in water without making muscle contractions or changes in position. Withdrawal from the water will be allowed if the patient can no longer tolerate the painful stimulus. This test will be conducted in a room with controlled room temperature, humidity, lighting, and noise.

Using a digital pressure algometer, the pressure pain threshold (PPT) will be performed in the forearm regions and tibialis anterior muscle of the dominant limbs before and after 1 min of the CPT. The tibialis anterior muscle and the distal part of the dorsal forearm, which had not been immersed in water, will be evaluated because of the lack of their relationship with the participants’ musculoskeletal complaints.

The operation of the pressure algometer and PPT measurement will be explained to the patients, and a practice test will be conducted on the patients’ dominant forearm to ensure that the test has been understood. Force will gradually be increased [1 kg-force/s] until the feeling of pressure changes to pain. The PPT will be recorded in kilograms force [Kgf]. The PPT will be repeated three times and the mean will be calculated to give the baseline PPT. The efficiency of the descending nociceptive inhibitory system will be evaluated by calculating the difference between PPT values in CPT (final cost − initial value) [41].

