The results will be considered clinically significant if a minimum difference of 10% change in PPT values in CPT is maintained at 6 months. Based on a previous study results [57] and a standardized mean score of 10 [58] on the letter–number sequencing subtask of WAIS-III, the mean reaction time for the Stroop interference effect will be fixed at approximately 230 s for the treatment to be considered successful. A reduction of 2 points on the NPRS [59], a cut-off value of 13, and a difference of 8 and 4 points will be considered as the minimal clinically important difference for the ODI [60], WHOQOL-BREF [61], and isometric muscle strength [62] respectively, which would indicate the success of the therapeutic intervention used.

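### The Outcomes section makes the primary endpoint CPM and pain together; the rest of the protocol, including the power calculation, makes it CPM alone

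*Protocol article*

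**What the plan says.** **Outcomes {12}.** "The primary efficacy endpoint will be a minimum difference of 10% change in PPT values in CPT and a difference of" at least 20% "from baseline to week 12 in the average daily score on an 11-point" NPRS. The list of secondary endpoints that follows covers executive function, strength, quality of life and disability. It does not include the NPRS.

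**Abstract, Methods.** "The primary outcomes are changes in CPM outcomes as measured by the cold pressor test (CPT"). Pain is on the other side of the line: "The secondary objectives are to evaluate executive functioning, pain, disability, quality of life, and spine muscle strength". Objectives {7} makes the same split.

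**Measure descriptions.** CPM is the only measure under the Primary outcome measure heading, where it is defined as final minus initial PPT within one cold pressor test. The NPRS is described after the Secondary outcomes heading, as a mark on a 0 to 10 scale.

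**Assessment times, Trial design {8}.** "An independent assessor will collect data at baseline (t0), after intervention at 3 months (t1), and at the 6-month follow-up (t2"). Section {18a} adds that all data are collected face to face.

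**Statistical methods {20a,b}.** "The results will be considered clinically significant if a minimum difference of 10% change in PPT values in CPT is maintained at 6 months". For pain, the success criterion is "A reduction of 2 points on the NPRS". The planned analysis is a repeated-measures ANOVA of means.

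**Sample size {14}.** 30 per group, 80 kPa difference in inhibition, SD 100 kPa, two-sided alpha 0.05, 87% power. This rises to 43 per group for 30% dropout.

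**The concern.** A trial that improves CPM but not pain is positive under the Abstract, the Objectives and the Primary outcome measure heading, and negative under Outcomes {12}. If this stays open, the choice between the two can be made after the results are known.

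Three features of the Outcomes sentence add to the difficulty:

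- It relies on a daily-average pain score, while the text describes ratings at three visits.
- Its NPRS threshold is worded differently from the one in the Statistical methods.
- Its CPM clause does not say whether the 10% is the PPT shift within one test or a change in that shift from baseline. On the first reading, a participant could meet it before any treatment.

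The power statement is also at stake, because it was worked out for one continuous variable.

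**Working it through.** **1. Reproduce the stated power (CPM alone).** Inputs from Sample size {14}: n = 30 per group, difference 80 kPa, SD 100 kPa, two-sided alpha 0.05.

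- Standardised difference = 80/100 = 0.8. Its standard error is sqrt(2/30) = 0.258.
- Normal approximation: 0.8/0.258 − 1.96 = 1.14, which gives power 0.873. The noncentral t gives 0.861. Both agree with the stated 87%.
- Dropout: 30/(1 − 0.30) = 42.9, so 43 per group. Four randomised groups give 4 × 43 = 172, as stated.

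The arithmetic is therefore right for CPM as a single continuous endpoint.

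**2. Power if both CPM and NPRS must succeed.** For any two criteria, P(both) ≤ min(P(CPM), P(NPRS)). If they are independent, P(both) = P(CPM) × P(NPRS). The protocol gives no NPRS SD, so the following rests on assumed SDs of 1.5 to 2.5 points and between-group differences of 1.0 to 2.0 points. Both components are taken as two-sided t-tests at 0.05 with 30 per group, and CPM power is 0.861.

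| NPRS SD | Difference | NPRS power | Joint power, independent | Upper bound |
|---|---|---|---|---|
| 1.5 | 1.0 | 0.719 | 0.619 | 0.719 |
| 1.5 | 1.4 | 0.945 | 0.814 | 0.861 |
| 1.5 | 2.0 | 0.999 | 0.861 | 0.861 |
| 2.0 | 1.0 | 0.478 | 0.412 | 0.478 |
| 2.0 | 1.4 | 0.760 | 0.655 | 0.760 |
| 2.0 | 2.0 | 0.968 | 0.834 | 0.861 |
| 2.5 | 1.0 | 0.332 | 0.286 | 0.332 |
| 2.5 | 1.4 | 0.569 | 0.490 | 0.569 |
| 2.5 | 2.0 | 0.861 | 0.742 | 0.861 |

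Joint power runs from 29% to 86% under independence. Positive correlation raises it towards the upper bound but not past it.

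**3. The two NPRS thresholds.** Table 2 requires a score above 4 at entry, so 5 to 10 in whole numbers. If 20% means percent of the participant's baseline:

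| Baseline | 20% in points | 2 points as % of baseline |
|---|---|---|
| 5 | 1.0 | 40.0 |
| 6 | 1.2 | 33.3 |
| 7 | 1.4 | 28.6 |
| 8 | 1.6 | 25.0 |
| 9 | 1.8 | 22.2 |
| 10 | 2.0 | 20.0 |

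The rules agree only at a baseline of 10. At a baseline of 5, a 1-point fall passes the first rule and fails the second. If 20% instead means 20% of the scale, 0.20 × 10 = 2 points and the rules coincide.

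**4. The daily score.** Trial design {8} has three assessments, {18a} has face-to-face collection, and the NPRS section describes a mark on the scale. The diaries in the text concern home exercise or treatment, not pain. No described procedure yields a daily pain average.

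**5. The 10% clause.** The CPM section computes final minus initial PPT within one test. The Outcomes wording refers to PPT values in the test, which fits that single-visit quantity as easily as a change between visits.

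**The case against.** The best defence is that one sentence departs from an otherwise consistent document. The Abstract, Objectives, Trial design, Primary outcome measure heading and sample size all point to CPM alone. This stands as a guide to what was probably intended, and the fix follows it. It does not remove the contradiction: the departing sentence is the one that formally defines the primary efficacy endpoint, and the NPRS is absent from the secondary list beside it.

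Other parts of the defence narrow the point:

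- **20% against 2 points.** These conflict only if 20% is a percentage of baseline. The wording allows a percentage of the scale, so this is an ambiguity to settle and not a proven contradiction.
- **Change over time.** The Abstract and Trial design speak of changes in CPM, which supports a change-from-baseline reading. The 10% clause is loosely worded and not shown to be wrong.
- **Daily score.** Table 1, the schedule, is not reproduced in the text available. A reader might infer that daily pain is never collected. The document supports only that no daily collection is described.

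A reader might infer three further things that the text does not support:

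- **The 6-month rule as another primary endpoint.** The Statistical methods present it as a condition for clinical significance, and the word maintained makes it a durability criterion.
- **Inflated type I error from several sites and visits.** PPT "will be performed in the forearm regions and tibialis anterior muscle of the dominant limbs", but nothing lets any one site or visit carry the claim. The Outcomes sentence joins its criteria with and, and a conjunction does not raise the error rate.
- **A defect in leaving open how sites are combined, or whether a responder test is run.** Both can properly be left to a statistical analysis plan.

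**Conclusion.** The point holds as an internal contradiction about what the primary endpoint is, and it must be fixed because it changes which result counts as positive. The 87% power is correct for CPM alone and does not apply to the conjunction. By how much it overstates power there cannot be known from the document. The 29% to 86% range depends on the assumed NPRS SDs and differences, on independence, and on treating both components as comparisons of means. Only the bound, the power of the weaker component, is free of those assumptions.

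The daily score, the NPRS threshold and the meaning of 10% are lesser points of wording in the same sentence and should be settled together with it.

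**What to change.** Reword Outcomes {12} and the success criteria in Statistical methods {20a,b}:

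1. State one primary endpoint: the between-arm difference in change from t0 to week 12 in the CPM effect (post-test minus pre-test PPT). The CPM effect is the continuous variable on which the sample size and the ANOVA already rest.
2. List the NPRS as secondary, using the rating taken at t0, t1 and t2, and delete the reference to a daily average.
3. Use one NPRS threshold in both sections, and say whether it is in points, percent of baseline or percent of the scale.
4. Describe the 10% and 6-month criteria as supportive statements of clinical relevance, with 10% defined as a change from baseline.

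When doing this, the sponsor should confirm that the 100 kPa SD, which is stated for the inhibitory effect, also serves for its change.

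The cost is rewording in two sections, with no new data and no extra visits. Section {11b} requires a formal amendment for changes to objectives or design, so review by both boards may be needed. It should be dated before any comparison between arms is seen.
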